#### Assignment of interventions: allocation

Potential participants and carers who fulfil all inclusion and meet no exclusion criteria will be informed of their screening results by local research staff and arrangements will be made for randomisation and treatment visits.

A web-based randomisation and back-up system will be provided by Sealed Envelop (https://sealedenvelope.com) based on a trial minimisation algorithm and randomisation list developed in consultation with a Swansea Trials Unit (STU) statistician. Participants will be assigned 1:1 to either the PES+EMDR group or TAU using IQ, PTSD status and gender as minimisation variables. The randomisation protocol will be implemented by the Trial Manager.

#### Assignment of interventions: blinding

Research assistants will be masked to allocation when completing outcome assessments. Given the nature of the intervention, it would be impossible for the clinical team to be blinded. The following safeguards have been implemented to maintain allocation concealment: (1) all PIs and sites have been directed not to discuss or disclose information about therapy to research assistants, (2) trial participants and their carers have been directed not to discuss or disclose information about therapy to research assistants, (3) research assistants have been located away from clinical teams (eg, within NHS Trust Research and Development offices) and (4) should inadvertent unmasking occur, research assistants will report that this has occurred immediately to the Trial Manager. When unmasking occurs, we will replace an unmasked research assistant with a masked research assistant who will then become responsible for data capture.

### Data collection and management

#### Plans for assessment and collection of outcomes

Clinical and health-economic assessments will be conducted by masked assessors, before randomisation and with follow-up at 4 (post-PES), 8 (post-EMDR) and 14 months. The 4-month and 8-month assessments may be delayed by up to a month (or exceptionally, 2 months for the 8-month assessment if the 4-month assessment was delayed); the 14-month assessment will not be delayed. Data collection can be conducted over multiple sessions with a trial participant if required. Data will be digitised and entered onto our REDCap data management system managed by the CTU.

#### Plans to promote participant retention and complete follow-up

The participants will receive extensive information about the trial set-up and requirements during recruitment. We will attempt to collect follow-up data from participants who discontinue from the intervention.

#### Data management

The trial electronic database will be managed and operated as required by Good Clinical Practice. The site investigator or delegate will record all trial data within our electronic database (REDCap) provided by CTU. A record of patients who were screened as ineligible and those who were eligible and invited to take part but did not consent will be kept. The PIs are responsible for keeping a list of all consented patients, via the enrolment log. The investigator will ensure accuracy, completeness and timeliness of the data entered into the database.

Data will be checked according to a trial Data Management Plan and queries will be generated and sent to the site investigator for response using the REDCap database. Corrections resulting from these queries will be confirmed and sent back to STU. The queries and their responses will be stored in the audit trail of the electronic database.

Data will be analysed at the end of the trial once the database has been locked.

#### Confidentiality

All trial participant data will be pseudonymised and individual records identified using a unique participant identification number (PIN). A copy of the PIN will be kept securely within the site Investigator Site File (ISF). Minimal identifiable data to link participants' names and their PINs will be stored separately from the ISF.

The ISF containing original signed consent forms will be kept in secure premises. Access to the ISF will be restricted to researchers working on the trial. Sponsor representatives and auditors authorised to access the file.

### Statistical methods for primary and secondary outcomes

#### Quantitative outcomes

The primary outcome will be assessed using an intention-to-treat analysis. Quantitative outcome measures will be analysed by analysis of covariance, adjusting for baseline values of the outcome and any variables used in the randomisation process. Secondary outcomes will be analysed using linear or logistic regression models as appropriate reflecting the distribution of the outcome variable. The treatment effect will be estimated as an adjusted difference between sample means, presented with 95% CIs and p values. A statistical and health economic analysis plan (SHEAP) will be produced and finalised before data lock.

#### Process evaluation

A process evaluation will follow UK Medical Research Council guidelines^62^ and will include:

Completion of a Template for Intervention Description and Replication proforma to specify the intervention.^63^A description of the procedures used as TAU.Analysis of the fidelity of treatment delivery (as described above) and adherence.Recording of inadvertent unblinding, trial-related adverse events and reasons for drop-out.Interview transcripts of patients’, therapists’ and carers’ views of the acceptability and efficacy of treatment, which will be subjected to a Thematic Analysis^64^ and to Framework Analysis^65^ for comparison.

#### Health economic outcomes

The health economic analysis will consist of a within-trial cost-effectiveness using cost–utility analysis of PES+EMDR versus TAU, assessed from the perspective of the UK NHS and personal social services (PSS) at 14 months follow-up.

Resource use and related costs of developing and delivering the intervention, including therapist training, will be recorded and measured. Due to the variability in the delivery of TAU across sites and participants, a bespoke questionnaire will be completed by research assistants to collect any psychological, psychologically informed or other treatment provided by members of the Learning Disability Team for participants allocated to TAU from patient records.

The costs (NHS, other health providers, social care) of supporting participants through the period of treatment will be collected using the Client Service Receipt Inventory–CSRI: ID version^66 67^ adapted for this trial. Resource use will be valued using the most up to date reference costs; otherwise, estimates from the literature, adjusted for inflation, will be used, as is standard for this tool. The CSRI-ID will be administered at baseline and 14-month follow-up.

Descriptive statistics will be used to summarise resource use, costs and outcomes by study arm. Incremental costs and quality-adjusted life-years (QALYs) will be analysed using appropriate regression methodology adjusting for stratification and minimisation variables. The net benefit framework will be used to assess the cost-effectiveness over a range of values for the QALY.

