### Trial design

This is a two-armed parallel single-blind multicentre randomised controlled clinical trial comparing EMDR/PES+TAU to TAU including an internal pilot. The participant allocation ratio is 1:1.

The internal pilot phase is 18 months and has the following objectives: (a) recruit 36 participants by 14 months and (b) complete the intervention with at least 6 participants by 18 months to test adherence and retention through the two phases of the intervention. Progress during the internal pilot phase will be monitored by the Trial Steering Committee (TSC) and the Data Monitoring and Ethics Committee (DMEC) who will report directly to the funder. Any difficulties in meeting these objectives will be reviewed, and if possible, an appropriate mitigation strategy will be developed and implemented.

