### Oversight and monitoring

#### Composition of the coordinating centre and oversight committees

The Trial Management Group meets monthly and comprises the chief investigator, sponsor representative, the trial manager and other CTU staff.

The Site Management Group meets fortnightly and comprises the chief investigator and coinvestigators and the trial manager and other CTU staff as well as all the research assistants and PIs.

The TSC comprises a chair, statistician, representative of a national charity, an EMDR expert, the coinvestigator who oversees PPI, the coordinator of a service-user PPI group, and a carer.

The DMEC, which is independent of the sponsor and competing interests, comprises a statistician (in the chair), a senior clinical psychologist and a representative of a national ID charity.

All members of both the TSC and DMEC have signed a relevant charter and agreed Terms of Reference.

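### A TAU-only extraction from patient records is given to research assistants, who are also the masked outcome assessors, with no separation by staff or timing

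*Protocol article*

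**What the plan says.** Under *Trial design*, the article states: "This is a two-armed parallel single-blind multicentre randomised controlled clinical trial". The section *Assignment of interventions: blinding* identifies who is blind: "Research assistants will be masked to allocation when completing outcome assessments". It adds: "Given the nature of the intervention, it would be impossible for the clinical team to be blinded". It then lists four safeguards. Investigators and sites must not talk about therapy to the assistants. Participants and carers must not either. Assistants are housed apart from clinical teams. Inadvertent unmasking is reported at once to the Trial Manager, and an unmasked assistant is replaced by a masked one.

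Under *Plans for assessment and collection of outcomes*, masking extends to the economic data: "Clinical and health-economic assessments will be conducted by masked assessors, before randomisation and with follow-up at 4 (post-PES), 8 (post-EMDR) and 14 months".

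Under *Health economic outcomes*, because TAU varies between sites and participants, "a bespoke questionnaire will be completed by research assistants to collect any psychological, psychologically informed or other treatment" that was "provided by members of the Learning Disability Team for participants allocated to TAU from patient records".

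**The concern.** The same job title carries two duties that do not fit together. One requires ignorance of allocation. The other is defined by allocation and has the person read clinical records, which can show the treatment delivered.

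At stake is the only blinding of outcome collection that the article describes. The clinical team is unblinded by necessity, and participants know whether they are receiving therapy. The primary outcome, the IES-ID, is self-reported by adults with intellectual disabilities, and collection may be spread over several sessions. An assessor who knows the allocation could, without intending to, explain, prompt or record items differently by arm. Masking guards against that. It does not guard against the participant's own expectation.

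**Working it through.** The article gives no figure on this point, so the check compares its sections.

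1. **Role.** The blinding section names research assistants as the masked assessors. The health economic section gives the TAU questionnaire to research assistants. No section describes a second, unmasked group with that title.

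2. **What the task needs.** The form is for TAU participants only. To complete it, someone must be told, or must find out, who is in TAU. The source is the patient record. The disclosure is therefore part of the task and does not depend on a slip by anyone.

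3. **Whether masking is required for it.** The questionnaire sits under the health economic methods, and the data collection section says masked assessors conduct health-economic assessments. On a plain reading the task falls within that statement, which a one-arm form cannot satisfy. Even if record extraction is not counted as an assessment, step 1 still conflicts with step 2.

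4. **Whether the safeguards reach it.** The first two restrain what other people say. The third separates assistants physically from clinical teams, but reading the record bypasses that separation. The fourth concerns inadvertent unmasking, as does the unblinding record in the process evaluation. None covers unmasking through a planned duty. If the duty is done while assessments are outstanding, the replacement rule would be triggered by routine work.

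5. **Whether staff or timing separate the two duties.** The health economic section gives no timing for the form, and the schedule in Table 1 does not list it.

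6. **What follows under each arrangement the text allows:**

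| Who extracts | When | Effect on assessor masking |
|---|---|---|
| Staff who collect no outcome data | Any time | None, if they do not pass it on |
| An assistant | After that participant's 14-month data are locked, with no affected assessments outstanding | None |
| An assistant | After that participant's last assessment, while still assessing others | None for that participant; others are exposed if the task shows their allocation, for example through a list of TAU participants |
| An assistant | While still assessing that participant | Allocation can be revealed: being asked for the form identifies TAU, and not being asked may suggest PES/EMDR |

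The article neither states nor excludes any of the four rows. Two of them breach the masking it promises.

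**The case against.** The best reply is that the text allows a harmless reading. Masking is promised for the time when outcome assessments are completed. There is more than one assistant, since one can replace another. The economic analysis is set at 14 months. Retrospective extraction after the last visit, or by an assistant who does not assess that participant, fits all of this. Staff delegation and form timing are also details that an article often leaves to the full protocol.

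Part of this stands. A reader might infer that the form reveals every participant's allocation and so defeats the blinding, TAU by presence of a form and PES/EMDR by absence. That requires the same person to assess and extract, and to extract before the last assessment. The article states neither. Absence of a form also tells an assistant nothing if forms are issued only after follow-up ends.

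A reader might see further leaks in the fortnightly Site Management Group, which includes "other CTU staff as well as all the research assistants and PIs", and in the lack of a stated order between the service-use inventory and the outcome scales. The documents do not support these as faults. The article gives only the group's membership, and investigators are directed not to disclose therapy to assistants. Participants and carers have the same direction, and the order of instruments within a visit is a working instruction.

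The appeal to missing detail does not dispose of the main point. The article chose to state who completes the form, for which arm and from what source, and that statement conflicts with its own blinding section.

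**Conclusion.** The point holds as a conflict in the text. A task that discloses allocation is assigned to the role that must be masked, and nothing separates the two by staff or time. This undermines assessor masking to the extent that any assistant extracts while still assessing.

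Its size cannot be computed. For a given assistant it runs from none of their participants, if extraction is late or done by others, to potentially all of them, if it is done during follow-up. The article gives no caseloads, staffing overlap or extraction dates to narrow that range. Any resulting bias in the IES-ID would arise through administration and recording only, because unblinded participants give the answers.

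The conclusion assumes that research assistants means the same staff group in both sections, as nothing in the article says otherwise.

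**What to change.** Amend *Health economic outcomes* to state one of two arrangements:

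- The record extraction is done by existing staff who collect no outcome data.
- It is done for each participant only after that participant's 14-month outcome data are entered and locked, by someone with no assessments outstanding for participants whose allocation the task would reveal.

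If either is already the practice, a sentence saying so resolves the conflict. Where extraction has been done otherwise, record each instance as unmasking and report the counts by arm. The adverse event section already provides an unblinding log that could hold these records.

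The cost is modest: extraction is bunched late in follow-up or moves to other staff. Recruitment began in March 2022, so the earliest participants could have reached 14 months around May 2023, and some extraction may already have taken place. Recruitment closed on 31 December 2024. If the last participant was randomised about then, the last 14-month visit falls around the end of February 2026. With completion expected in July 2026, that leaves roughly five months for late extraction, or less if randomisation ran later.

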**Methods:**

This is a two-arm parallel single-blind randomised controlled trial comparing PES-EMDR+TAU to TAU including an internal pilot phase. Outcome data will be captured prior to randomisation, and at 4 (after PES), 8 (after EMDR) and 14 months postrandomisation by masked assessors. 144 adults with intellectual disabilities with a diagnosis of PTSD will be allocated (1:1) randomly using minimisation from National Health Service (NHS) community and inpatients services for adults with intellectual disabilities in England. Participants are eligible to take part in this trial if: (1) they are aged 18 or older, but younger than 66, (2) have a Full Scale IQ<75, (3) meet diagnostic criteria for PTSD and (4) have suffered a major identified trauma at least a year earlier and (5) are able to communicate using English and have capacity to consent to take part in this clinical trial. Participants allocated to the active intervention will receive 10 sessions of PES, followed by up to 15 sessions of EMDR alongside TAU. The active intervention is being delivered by psychologists experienced in working with adults with intellectual disabilities who have received additional intervention training. TAU is likely to include medication, behaviour support plans designed to target challenging behaviour, or non-trauma-focused psychological interventions. The primary outcome is a measure of PTSD symptoms. Secondary outcomes are other mental health problems, including anxiety and depression, challenging behaviour, participant and carer QoL, and carer burden. We are also capturing cost data to allow for a cost–utility analysis. A process evaluation will be completed using data generated from semistructured interviews with a sample of participants, therapists and carers alongside the capture of fidelity and adherence data.

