#### Relevant concomitant care permitted or prohibited during the trial

Participants can receive any concomitant care considered suitable by their clinical team other than another trauma-focused psychological therapy.

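### Learning Disability Team treatment is extracted from patient records in the TAU arm only, although both arms receive TAU, so incremental cost is liable to be understated for PES/EMDR

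*Protocol article*

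**What the plan says.** The trial compares PES/EMDR plus TAU with TAU. The abstract's Methods paragraph says: "Participants allocated to the active intervention will receive 10 sessions of PES, followed by up to 15 sessions of EMDR alongside TAU". The section on concomitant care sets one rule for everyone: "Participants can receive any concomitant care considered suitable by their clinical team other than another trauma-focused psychological therapy".

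Under Health economic outcomes, resource use comes from three sources:

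- The cost of developing and delivering the intervention, including therapist training.
- A records questionnaire, introduced with its reason: "Due to the variability in the delivery of TAU across sites and participants, a bespoke questionnaire will be completed by research assistants". It covers psychological, psychologically informed and other treatment "provided by members of the Learning Disability Team for participants allocated to TAU from patient records".
- The CSRI-ID, with no restriction by arm: "The costs (NHS, other health providers, social care) of supporting participants through the period of treatment will be collected using the Client Service Receipt" Inventory, in a version adapted for the trial. On timing, the text says: "The CSRI-ID will be administered at baseline and 14-month follow-up".

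The allocation section settles what being allocated to TAU means: "Participants will be assigned 1:1 to either the PES+EMDR group or TAU". It is the control arm.

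**The concern.** The reason given for the questionnaire is that TAU varies between sites and participants. That applies just as much to the TAU part of the PES/EMDR arm, yet the form is not completed there. The therapists' session forms (Fidelity and adherence) and the intervention costing cover PES and EMDR only. For other contacts with the Learning Disability Team in the PES/EMDR arm, the CSRI-ID is the only source of cost data described.

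Two things are at stake. First, cost-effectiveness is part of the primary objective, and the plan is to carry incremental cost into a net-benefit analysis. Care found in one arm and missed in the other enters that difference directly. Second, another trauma-focused therapy is barred in both arms, and the article says that such therapies have become more common since the trial was designed. Whether co-treatment differed between arms is therefore a fair question, but patient records would be searched for it in one arm only.

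This is a stated collection rule, so it is not a detail left to the statistical and health economic analysis plan. That plan can decide how sources are combined, but it cannot supply data that were never extracted.

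**Working it through.** **Inputs.** The documents give 144 participants, 1:1 allocation, a 14-month horizon, and which source applies to which arm. They give no cost, number of contacts or capture rate, so there is no figure of the plan's own to reproduce. The following are unknowns:

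- m_E and m_T: true mean cost per participant of team-delivered TAU in the PES/EMDR and TAU arms.
- c: share of that cost captured by the CSRI-ID, taken as equal in both arms.
- r: share captured by patient records.

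The true contribution of team TAU to incremental cost (PES/EMDR minus TAU) is m_E − m_T. Bias is observed minus true.

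**Case A: records bring the TAU arm up to complete data.** The observed difference is c·m_E − m_T, so

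bias = (c·m_E − m_T) − (m_E − m_T) = −(1 − c)·m_E.

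The TAU arm is then measured correctly. The error is the care missed in the PES/EMDR arm, so its size depends on m_E and not on how many extra contacts the records reveal among controls.

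**Case B: records are added to the CSRI-ID in the TAU arm, so shared contacts count twice.** The observed difference is c·m_E − (1 + c)·m_T, so

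bias = −(1 − c)·m_E − c·m_T.

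**Results in units of m_E:**

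| c | Case A | Case B, m_T = m_E | Case B, m_T = 2·m_E |
|---|---|---|---|
| 0 | −1.00 | −1.00 | −1.00 |
| 0.25 | −0.75 | −1.00 | −1.25 |
| 0.50 | −0.50 | −1.00 | −1.50 |
| 0.75 | −0.25 | −1.00 | −1.75 |
| 1 | 0 | −1.00 | −2.00 |

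**Case C: records replace the CSRI-ID in the TAU arm and are themselves incomplete.** The observed difference is c·m_E − r·m_T, so

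bias = −(1 − c)·m_E + (1 − r)·m_T.

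With m_T = m_E this is (c − r)·m_E, which is positive when the records capture less than the CSRI-ID. The sign can therefore reverse.

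**Effect on net benefit.** Net benefit is the value per QALY times incremental QALYs, minus incremental cost. Its bias is the cost bias with the sign changed, +(1 − c)·m_E in Case A, at every value placed on a QALY.

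**After the fix.** With records as the single source in both arms, the observed difference is r·(m_E − m_T), and the bias is −(1 − r)·(m_E − m_T). This is zero if the records are complete (r = 1), and also zero if the arms use equal amounts of team care.

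**What the article suggests about c.** Adding a records form because TAU varies suggests that the CSRI-ID was not thought sufficient on its own. Table 1 lists the CSRI-ID under the carer heading, while patients without a carer can be included. Both point to c below 1, but neither gives its value.

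**The case against.** The strongest reply is that the questionnaire is the comparator's counterpart to the intervention costing: each arm's main psychological treatment is measured in detail, and the CSRI-ID serves both arms as the common instrument. The adapted CSRI-ID is not shown and may ask fully about team contacts. As far as its columns can be read, Table 1 also places the CSRI-ID in both treatment phases, not only at baseline and 14 months; shorter recall would raise c. The two statements of timing need reconciling in any case. Finally, m_E may be small: people in therapy who are unwilling to pause it are excluded, and PES/EMDR takes up much of the treatment period.

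This bears on the size of the bias. It does not remove the asymmetry, because intervention costing does not cover background team care in the PES/EMDR arm, and no records-based source is described there.

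The reply also rules out several stronger inferences that a reader might draw:

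- That the cost estimate is certainly biased, always towards PES/EMDR. Case A gives zero at c = 1, and Case C can reverse the sign.
- That double counting will occur. The article does not say how the sources are combined, and that rule properly belongs in the analysis plan, which is not shown.
- That co-treatment cannot be examined at all in the PES/EMDR arm. The CSRI-ID covers both arms, Table 1 records concomitant medication without restriction by arm, and the process evaluation plans a description of TAU.
- That the treatment effect on PTSD symptoms is biased. The IES-ID and its analysis do not use these data.

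**Conclusion.** The point holds as one of unequal measurement. Team-delivered background care is ascertained from two sources in the TAU arm and, as far as described, from one in the PES/EMDR arm, for a reason that applies to both.

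Incremental cost is liable to be understated by (1 − c) × m_E, most likely in favour of PES/EMDR. If the records complete the TAU arm and nothing is counted twice, this runs from nil to the full mean team TAU cost in the PES/EMDR arm. It rests on the assumptions that c is the same in both arms and that the records are at least as complete as the CSRI-ID. The documents do not allow an amount in pounds. The second consequence is narrower: non-trial psychological treatment, including the barred trauma-focused therapy, may be less fully described in the PES/EMDR arm and cannot be compared on equal terms.

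Severity is moderate. Cost-effectiveness is in the primary objective, but the size is unknown and may be nil. It is best labelled a cheap improvement.

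**What to change.** In Health economic outcomes, replace the restriction to participants allocated to TAU with wording that covers all participants in both arms. Specify also:

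1. The same form, the same record source and the same 14-month window in both arms.
2. Trial PES and EMDR sessions are kept apart from background care and taken from the therapists' online session forms.
3. Learning Disability Team contacts are costed from one source in both arms, so that none is counted again through the CSRI-ID.
4. Extraction is done by existing staff who do not assess that participant's outcomes, or after the participant's last outcome visit. Patient records reveal allocation, and under the present rule so does the mere existence of a form, while research assistants are meant to stay masked.

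The cost is about 144 / 2 = 72 further record extractions with an existing form. They are retrospective and need no participant contact. Recruitment closed on 31 December 2024 and completion is expected in July 2026, so the work can still be done but must precede data lock.

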### Participant timeline

Our participant schedule of events and schedule of outcome assessments is found within table 1.

**Table 1 T1:** Schedule of events and outcome assessments

	Study period							
	Referral/clinic prescreening* (≤12 weeks)	Screening (<4 weeks)	Baseline Week 0	Phase 1 (PES/TAU) Weeks 5–16		Phase 2 (EMDR/TAU) Weeks 17–27		Follow-up Week 60
Week	**≤–12**	**–4**	**0**	**5–15**	**16**	**17–27**	**28**	**60**
Participant and carer								
Clinical history	Y							
Patient information	Y							
Participant								
Consent		Y						
Diagnostic interview		Y						
Diagnostic review		Y						
Concomitant medication		Y		Y	Y	Y	Y	Y
Confirm eligibility		Y						
Randomisation			Y					
Treatment (1–10 sessions for phase 1 and phase 2)				Y	Y	Y	Y	
Adverse events				Y	Y	Y	Y	Y
Subjective Units of Distress Scale (SUDS)				Y	Y	Y	Y	Y
IQ (WASI-II)		Y						
PTSD History (TIF)		Y						
PTSD Diagnosis/Complexity (ITQ-ID)		Y		Y	Y	Y	Y	Y
Self-reported questionnaires*†			Y		Y		Y	Y
Carer								
Adaptive Behaviour Assessment System - III (ABAS-III)		Y						
Carer-reported questionnaires‡			Y		Y		Y	Y
Self-reported questionnaires§			Y		Y		Y	Y
Service/Support Costs (CSRI-ID)			Y	Y		Y		Y
Audio recording	With participants' consent, one treatment session from phase 1 and phase 2 will be recorded with scoring using the EMDR Fidelity Rating Scale							
Interview	In line with qualitative recruitment methods, around 10 each of patients, carers and therapists will be interviewed about their experiences following completion of therapy.							

All visits are anticipated to take place in clinic or community settings, although other scenarios are permissible as required

* Completed assessments must be within 12 weeks of screening

† Patient completed self-reported questionnaires consist of IES-ID, GDS, GAS, PWI-ID

‡ Questionnaires completed by the carer regarding the participant: MPAS-ID, LANTS, ABC.

§ Questionnaires completed by the carer about their own well-being: SF-12, WEMWBS

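### The text gives the CSRI-ID at baseline and 14 months only, against four occasions in Table 1; if the text is followed, wider health and social care use during treatment rests on one form at week 60

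*Protocol article*

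**What the plan says.** Three parts of the protocol article bear on when cost data are collected.

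- **Health economic outcomes.** The analysis is a cost–utility analysis "assessed from the perspective of the UK NHS and personal social services (PSS) at 14 months follow-up". The NHS, other-provider and social care costs "of supporting participants through the period of treatment will be collected using the Client Service Receipt Inventory" in its intellectual disability version. The same paragraph then fixes the timing: "The CSRI-ID will be administered at baseline and 14-month follow-up".
- **Participant timeline, Table 1.** The row "Service/Support Costs (CSRI-ID", listed under the carer heading, is marked at week 0, once in the columns under "Phase 1 (PES/TAU) Weeks 5–16" (weeks 5–15), once under "Phase 2 (EMDR/TAU) Weeks 17–27" (weeks 17–27), and at week 60. Its cells for weeks 16 and 28 are blank, although the carer questionnaires are marked there.
- **Data collection and management.** Its subsection on assessing and collecting outcomes says: "Clinical and health-economic assessments will be conducted by masked assessors, before randomisation and with follow-up at 4 (post-PES), 8 (post-EMDR) and 14 months", without naming the instrument.

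The Health economic outcomes section also names two other cost sources. Resources for developing and delivering the intervention, including training, are recorded directly. For participants allocated to TAU, treatment given by the Learning Disability Team is taken from patient records with a separate questionnaire. No recall window for the CSRI-ID is given.

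**The concern.** The article gives two incompatible schedules for the CSRI-ID, and a third statement about health-economic assessments that matches neither exactly. A site or research assistant following the text would collect one form after baseline. One following Table 1 would collect three.

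The difference matters because the CSRI-ID is the only stated source for service use outside the intervention itself and outside TAU-arm Learning Disability Team treatment: inpatient care, other health providers and social care. Cost-effectiveness is part of the primary objective. If the two-occasion text is what happens, use of these services during treatment is either recalled from far back or falls outside the form's window. An analysis plan finalised before data lock cannot recover forms that were never completed.

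**Working it through.** **Occasions, side by side**

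| Source in the article | Occasions | Times |
|---|---|---|
| Health economic outcomes (names the CSRI-ID) | 2 | baseline, 14 months |
| Table 1 (names the CSRI-ID) | 4 marked columns | week 0, weeks 5–15, weeks 17–27, week 60 |
| Plans for assessment and collection of outcomes (health-economic assessments, instrument not named) | 4 | baseline, 4, 8, 14 months |

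The count of 2 in the text cannot be reproduced from the article's own schedule, which gives 4. The Table 1 row has one cell for each of the eight schedule columns, so the mismatch is not an effect of the table layout.

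**Distance from treatment to the last form.** Table 1 marks treatment from week 5 to week 28, and the last form at week 60.

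- End of treatment to form: 60 − 28 = 32 weeks.
- Start of treatment to form: 60 − 5 = 55 weeks.

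**Coverage under the two-occasion text.** The recall window is an assumption, taken from 3 to 14 months because the article states none. Let w be the window in weeks (months × 365.25 / 12 / 7).

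- Window starts at week s = max(0, 60 − w).
- Share of the 60 weeks not covered = s / 60.
- Share of treatment covered = max(0, 28 − max(5, s)) / (28 − 5).

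| Assumed window | Starts at week | 60 weeks not covered | Treatment weeks 5–28 covered |
|---|---|---|---|
| 3 months | 47.0 | 78% | 0% |
| 6 months | 33.9 | 57% | 0% |
| 9 months | 20.9 | 35% | (28 − 20.9)/23 = 31% |
| 12 months | 7.8 | 13% | (28 − 7.8)/23 = 88% |
| 14 months | 0 | 0% | 100% |

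**Check on the week numbering.** Table 1 places the post-EMDR assessment at week 28, while the data-collection section places it at 8 months. With treatment ending at 8 months, a 6-month window at month 14 reaches back to 14 − 6 = month 8, so it still covers no treatment up to that point. The result for short windows does not depend on which numbering is used.

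**After alignment.** With four occasions, the longest gap between forms falls from 60 weeks to 60 − 28 = 32 weeks if the third form is at the week 28 visit. If it is given as early as week 17, as Table 1's column allows, the gap is 60 − 17 = 43 weeks. In calendar months the gaps are 4, 4 and 6.

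**The case against.** Several objections have force.

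- **Other sources cover much of the treatment-phase cost.** A reader might infer that all treatment-period costs are at risk. The article does not support that: intervention delivery and training are recorded directly, and TAU-arm Learning Disability Team treatment comes from records. These are the costs one would most expect to separate the arms. This stands and narrows the point to wider health and social care use. It does not remove it, because inpatient, other-provider and social care use have no other stated source in either arm. The records extraction is also described only for those allocated to TAU, although the active arm receives TAU as well.
- **The recall window may be long.** It is tempting to say that 57–78% of the cost period goes unmeasured. That holds only for an assumed window of 3 to 6 months; at 14 months nothing is uncovered. The form is adapted for this trial, and an article may leave the window to the full protocol, so its absence is not itself a fault.
- **The respondent.** A reader might picture participants with intellectual disabilities recalling 60 weeks of service use. Table 1 lists the form under the carer. The supportable concern is that the attending carer may differ between visits, and that participants without a carer are admitted, both of which the carer eligibility section allows.
- **The data-collection section does not name the CSRI-ID.** That is correct. Only two schedules are stated for the instrument itself; the third statement is context that agrees with Table 1 on the number of occasions.
- **Table 1 may already be the practice.** If so, no data are lost and only a sentence is wrong. The article does not say which schedule is followed.

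**Conclusion.** The contradiction is certain: two CSRI-ID occasions in the text, four in Table 1, and four health-economic assessment times in the data-collection section. The consequence is conditional on the two-occasion text being what sites follow. In that case, health and social care use other than intervention delivery and TAU-arm Learning Disability Team treatment is captured for the treatment period only by a form about 32 weeks after treatment ends. That form covers from 0% of treatment weeks 5–28 (3- or 6-month window) to 100% (14-month window), and the full coverage depends on long carer recall.

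Incremental costs may then be incomplete or biased. The article does not show that they would be wrong, that recall error would differ between the arms, or that the exposed costs are where the arms differ most. The analysis of the IES-ID primary outcome is unaffected. The point is still worth settling before data lock, because cost-effectiveness belongs to the primary objective and the remedy is cheap.

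**What to change.** State which schedule has been used in practice, and reconcile the Health economic outcomes text, Table 1 and the data-collection section to four occasions: the CSRI-ID at baseline and at the existing 4-, 8- and 14-month visits. Each follow-up form should cover the time since the previous one, and the recall window should be stated. In Table 1 the two in-treatment marks would move to the week 16 and week 28 columns, where the other questionnaires already sit.

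Recruitment closed on 31 December 2024, so the earlier visits will be past for many participants. Asking them at the next visit to cover the whole gap would bring back the long recall at issue. For those whose earlier forms were not collected:

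- report how many there are, by arm;
- use available clinical records for the missing period, by the same rule in both arms;
- run a sensitivity analysis of incremental cost for these cases.

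The cost is one extra form at up to two visits that already take place, record extraction for those with missing forms, and a little more analysis. The last interval, from 8 to 14 months, still asks for about 6 months of recall.
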